### Study interventions

2.6

Following enrollment, all patients will receive a PBF during the run-in phase (study days 1–3). On study day 4, gastrointestinal function will be reassessed. Participants meeting AGI grade 0–I criteria are randomized (1:1) to one of two intervention arms: continuous Peptide-Based Enteral Formula Group (PBF group) and Sequential Standard Polymeric Enteral Formula Group (SPF group). All other aspects of ICU care follow contemporary best practice and local guidelines. Table 1 shows the schedule of enrolment, interventions, and assessments based on the SPIRIT 2013 statement (14). Detailed reporting checklists are provided in the Supplementary Table S2 (SPIRIT 2013 checklist).

**Table 1 tab1:** Schedule of enrolment, interventions, and assessments.

[figure not shown]

PBF group, Continuous Peptide-Based Enteral Formula Group; SPF group, Sequential Standard Polymeric Enteral Formula Group.

#### Arm#1: continuous Peptide-Based Enteral Formula Group (PBF group)

2.6.1

Intervention. Continue the PBF initiated during the run-in phase.

Administration mode. Continuous pump infusion via gastric (preferred) or post-pyloric feeding tube.

#### Arm#2: Sequential Standard Polymeric Enteral Formula Group (SPF group)

2.6.2

Intervention. Transition from a PBF to an SPF after randomization.

Administration mode. Continuous pump infusion (gastric or post-pyloric).

#### General management

2.6.3

All other aspects of patient management will follow standard clinical practice. This includes, but is not limited to, monitoring of vital signs, feeding tolerance, laboratory testing, fluid resuscitation, mechanical ventilation, and vasopressor support, as deemed necessary by the attending clinical team. No study-directed interventions will be applied to any domain of care other than nutritional support. All concomitant treatments will be determined by the responsible clinicians and documented in the medical record.

Nutrition protocol. Enteral nutrition will be delivered in accordance with the 2019 European Society for Clinical Nutrition and Metabolism (ESPEN) guidelines (15). Because indirect calorimetry is not used in this study, the energy target will be set using a simplistic weight-based equation of 25–30 kcal/kg/day consistent with the 2016 ASPEN guideline (12) and several large clinical studies (17, 18), The protein target is 1.3 g/kg/day (15). For patients with obesity Body Mass Index (BMI) ≥ 30 kg/m^2^, adjusted body weight (AdjBW) will be used for energy and protein calculations, as recommended by 2019ESPEN guidelines (15). AdjBW = Ideal Body Weight (IBW) + 0.33 × (Actual Body Weight − IBW), where IBW is estimated using a BMI-based method [IBW = 2.2 × BMI + 3.5 × BMI × (height – 1.5 m)].

Food intolerance (FI) will be defined in accordance with the terminology and definition framework proposed by the ESICM (6) Working Group on Abdominal Problems in 2012. FI management in both groups will be conducted in accordance with the recommendations of the 2022 Evidence-Driven Feeding Guidelines for Nutrition in Critically Ill Patients (NEED) (17).

Parenteral nutrition (PN). In patients who do not tolerate full-dose enteral nutrition during the first week in the ICU, the safety and potential benefits of PN will be assessed case-by-case, with the final decision made by the attending physician.

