#### Primary outcome definition and measures

2.7.1

Energy intake on Day 7, defined as the actual caloric intake on study Day 7 (kcal/kg/day). For patients with BMI > 30 kg/m^2^, an adjusted body weight will be used.

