#### Secondary outcome definition and measures

2.7.2

Protein intake on Day 7, defined as the actual protein delivered on study Day 7 (g/kg/day). For patients with BMI > 30 kg/m^2^, an AdjBW will be used.Occurrence of FI between ICU days 4–7, FI is defined as (6) present if any of the following criteria are met: ① Vomiting: any visible regurgitation of gastric contents, irrespective of volume. ② High gastric residual volume (GRV): any single GRV > 200 mL. ③ Diarrhea: ≥3 loose or liquid stools per day and stool weight >200–250 g/day or volume >250 mL/day. ④ Gastrointestinal (GI) bleeding: any intraluminal GI bleeding confirmed by gross blood in vomitus, gastric aspirate, or stool. ⑤ Insufficient enteral energy delivery: failure to achieve ≥20 kcal/kg body weight/day via the enteral route within 72 h after initiation/attempt of enteral feeding. ⑥ Cessation of enteral nutrition: enteral feeding discontinued for any clinical reason. Outcome recording. The presence or absence of FI will be assessed once per day on ICU days 4–7. In addition to the composite FI outcome, individual FI components will be reported and analyzed separately.Change in nutritional biomarkers. Defined as serum albumin and prealbumin concentrations measured on study day 1 (baseline) and day 7. Reporting values (albumin in g/L; prealbumin in mg/L) at each time point; change calculated as Day 7 − Day 1.Skeletal muscle status. Muscle mass change will be assessed using the following sonographic metrics on ICU days 1, 4, and 7 after admission: upper-limb muscle thickness; quadriceps muscle thickness; rectus femoris cross-sectional area (RF-CSA).Intestinal injury biomarkers. Between-group differences in intestinal injury markers will be evaluated using serum/plasma concentrations of D-lactate, intestinal fatty-acid binding protein (I-FABP), and diamine oxidase (DAO) on study Day 1 and Day 7. *Measurement & reporting:* assays performed per manufacturer instructions; values reported in assay-specified units. Changes from baseline (Day 7–Day 1) and between-group differences in change will be analyzed.New infections in the ICU: Defined as infections newly acquired ≥48 h after ICU admission.ICU length of stay.Ventilator-free days: Ventilator-free days within 28 days in the ICU.ICU hospitalization cost. Defined as the total direct medical cost accrued during the index ICU stay, from ICU admission (time 0) to ICU discharge. Extracted from the hospital billing system/financial data warehouse using patient identifiers and ICU encounter numbers.28-day mortality: Assessed on day 28 after ICU admission.90-day mortality: Assessed on day 90 after ICU admission.

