#### Data analysis

2.8.2

All statistical analyses will be conducted in accordance with a pre-specified statistical analysis plan. The primary analysis will follow the intention-to-treat (ITT) principle The Full Analysis Set (FAS) will include all participants who were successfully randomized and entered the intervention period, provided that they have a valid assessment of the primary outcome (caloric intake on day 7) or sufficient information to derive this value. The Per Protocol Set (PPS) will be a subset of the FAS, including participants who received the allocated intervention for at least 72 h and had no major protocol deviations. The PPS will be used for sensitivity analyses to assess the robustness of the primary findings. The SS will include all participants who received at least one dose of the study intervention and will be used for safety analyses.

The primary outcome, caloric intake on day 7 (continuous variable), will be analyzed using a linear regression model. The model will include the intervention group and the predefined covariates (APACHE II score, BMI, AGI grade, and primary diagnosis) as fixed effects. As this is a single-center randomized controlled trial, no random effects will be specified. To account for potential model misspecification and heteroscedasticity, heteroskedasticity-robust (sandwich) standard errors will be used for statistical inference. If the model residuals show substantial deviation from normality or are influenced by outliers, data transformation (for example, logarithmic transformation) or a nonparametric bootstrap method will be applied in sensitivity analyses to assess the robustness of the results.

Continuous secondary outcomes (e.g., the number of days without a ventilator in the ICU) will be analyzed analogously using linear regression models; secondary binary outcomes (e.g., FI) will be analyzed using a generalized linear model (GLM) with a logit link function. The model will include the intervention group and the pre-specified covariates as fixed effects. As this is a single-center study without inter-center or clustering structures, no random effects will be specified. In addition, because FI is a composite secondary endpoint, each FI component will be reported and analyzed separately alongside the composite FI outcome.

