#### Missing data and interpolation strategies

2.8.3

The proportion of missing data for the primary outcome (caloric intake on day 7) is expected to be approximately 15%, mainly due to discharge, transfer, or incomplete records. The primary analysis will be conducted in the FAS using multiple imputation (MI) under the missing-at-random (MAR) assumption. The imputation model will include treatment group, APACHE II score, BMI, AGI grade, primary diagnosis, and other variables related to missingness or the outcome.

As sensitivity analyses, a complete-case analysis (including only participants with observed day-7 outcomes) will be performed. In addition, PPS analysis and delta-adjusted MI analyses will be conducted to assess the robustness of the results under alternative missing data assumptions.

If the results are consistent across analyses, the study findings will be considered robust.

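### The ideal-body-weight equation does not say which BMI to enter; with the patient's own BMI it returns roughly actual weight and cancels the obesity adjustment

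*Protocol article*

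**What the plan says.** Section 2.6.3 (General management, Nutrition protocol) introduces the rule and the abbreviation together: "For patients with obesity Body Mass Index (BMI) ≥ 30 kg/m^2^, adjusted body weight (AdjBW) will be used for energy and protein calculations". It then defines the weight as "AdjBW = Ideal Body Weight (IBW) + 0.33 × (Actual Body Weight − IBW". The ideal weight in that formula is specified in turn: "where IBW is estimated using a BMI-based method [IBW = 2.2 × BMI + 3.5 × BMI × (height – 1.5 m". No target, ideal or reference BMI is named there or anywhere else in the article.

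The adjusted weight has two uses:

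- **Targets.** It is multiplied by 25–30 kcal/kg/day and 1.3 g/kg/day to set energy and protein goals (section 2.6.3).
- **Outcomes.** It is the per-kilogram denominator for obese patients in the primary outcome, day-7 energy intake ("an adjusted body weight will be used", section 2.7.1), and in day-7 protein intake ("an AdjBW will be used", section 2.7.2).

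Elsewhere BMI is plainly the patient's own value: in the obesity cut-offs, in the primary model of section 2.8.2 ("the predefined covariates (APACHE II score, BMI, AGI grade, and primary diagnosis"), and in the handling of missing data in section 2.8.3 ("The imputation model will include treatment group, APACHE II score, BMI, AGI grade, primary diagnosis").

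The cut-off is BMI ≥ 30 in section 2.6.3 but BMI > 30 in sections 2.7.1 and 2.7.2.

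**The concern.** An equation of this form converts a BMI and a height into a weight. It gives an ideal weight only if the BMI entered is an ideal one. If the patient's own BMI goes in, the patient's own weight should come out, and the correction towards ideal weight disappears.

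Two things are at stake. First, anyone who follows the printed equation would feed obese patients to a target based on roughly actual weight, in a population recovering from gastrointestinal injury. Second, the primary outcome in these patients would be divided by an unadjusted weight reported as adjusted. If bedside staff and analysts read the term differently, targets and outcomes would rest on different weights, and nothing in the data would flag it.

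**Working it through.** **Inputs.** From section 2.6.3: the IBW equation, the 0.33 factor, and the targets of 25 kcal/kg (lower end) and 1.3 g/kg. From section 2.5: the planned difference, 24.9 − 22.4 = 2.5 kcal/kg/day. The article gives no worked IBW or AdjBW, so there is no printed figure to reproduce. Assumptions not in the article: a reference BMI of 22 or 25, the example patients, the obese share, and how far delivery responds to the target.

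**Step 1: the patient's own BMI.** Let B be BMI and h height in metres.

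- Actual weight = B·h²
- IBW = 2.2B + 3.5B(h − 1.5) = B(3.5h − 3.05)
- Actual − IBW = B(h² − 3.5h + 3.05) = B[(h − 1.75)² − 0.0125]
- AdjBW/actual − 1 = −0.67 × [(h − 1.75)² − 0.0125]/h²

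B cancels from the last line, so the result is the same at any degree of obesity.

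| Height (m) | AdjBW relative to actual weight |
|---|---|
| 1.50 | −1.49% |
| 1.60 | −0.26% |
| 1.70 | +0.23% |
| 1.75 | +0.27% |
| 1.80 | +0.21% |
| 1.90 | −0.19% |

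**Step 2: one patient, 1.70 m, BMI 35.** Actual weight = 35 × 2.89 = 101.15 kg.

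| BMI entered | IBW (kg) | AdjBW (kg) | × 25 kcal/kg | × 1.3 g/kg |
|---|---|---|---|---|
| Own (35) | 77.0 + 24.5 = 101.5 | 101.5 + 0.33 × (−0.35) = 101.38 | 2535 | 131.8 |
| Reference 22 (assumed) | 48.4 + 15.4 = 63.8 | 63.8 + 0.33 × 37.35 = 76.13 | 1903 | 99.0 |
| Reference 25 (assumed) | 55.0 + 17.5 = 72.5 | 72.5 + 0.33 × 28.65 = 81.95 | 2049 | 106.5 |

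With own BMI, the ideal weight slightly exceeds the actual weight of an obese patient. The energy target is 486 to 631 kcal/day higher than under the reference readings.

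**Step 3: bedside and analysis read it differently.** Same patient, target fully delivered. If the ward uses own BMI and the analyst a reference BMI, a 25 kcal/kg target is recorded as 2535/81.95 = 30.9 to 2535/76.13 = 33.3 kcal/kg. In the reverse case it is recorded as 1903/101.38 = 18.8 to 2049/101.38 = 20.2 kcal/kg.

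**Step 4: effect on the between-arm difference.** Take 1.70 m and BMI 33. AdjBW is 95.59 kg with own BMI, 74.22 kg with reference 22 and 80.05 kg with reference 25. The ratio R of own-BMI to reference weight is 1.288 or 1.194, and the 25 kcal/kg target is 534 or 389 kcal/day higher. If a fraction f of that increase is actually delivered, kcal/kg is multiplied by [1 + f(R − 1)]/R. The shrinkage per obese patient is therefore (1 − f)(1 − 1/R). With an assumed 10% obese share and the same treatment difference in obese and other patients:

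| f | Per obese patient (ref 25 to ref 22) | Overall, 10% obese |
|---|---|---|
| 1 | 0% | 0% |
| 0.5 | 8.1–11.2% | 0.8–1.1% |
| 0 | 16.3–22.4% | 1.6–2.2% (0.04–0.06 of 2.5 kcal/kg) |

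At f = 0 and an obese share of 5–20%, the overall shrinkage is 0.8–4.5%, or 0.02–0.11 of 2.5 kcal/kg.

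**The case against.** The strongest reply is that a target BMI was obviously meant. The quantity is called an ideal weight and is subtracted from actual weight, which is pointless if the two are equal. The section cites a guideline for the adjustment, and the full protocol may hold the constant. On that view this is a missing label, and nothing shows that anyone will enter the patient's own BMI. The intent is probably as described. However, the article prints the equation, and under its own use of the abbreviation the equation fails. The number is needed on either reading: moving from 22 to 25 alone shifts AdjBW by 81.95 − 76.13 = 5.8 kg in the example.

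The second reply is that the trial's answer barely moves. That stands. Both arms use the same rule, the shrinkage is small, and BMI in the primary model may absorb part of the change in scale. No effect on the standard deviation or power was worked out. A wrong denominator can also be corrected at analysis, since the outcome can be recomputed from recorded intake, weight and height. A bedside target already delivered cannot be.

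The cut-off mismatch matters only at a BMI of exactly 30 and carries no weight in the conclusion.

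**Conclusion.** The concern holds. As printed, and with BMI meaning what it means in the rest of the article, the obesity adjustment has no practical effect. This is algebra and rests on no assumption beyond which BMI is entered.

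The size of the consequences is conditional. Against an assumed reference BMI of 22–25, literal use raises the energy target of an obese patient of 1.70 m by about 390–530 kcal/day at BMI 33 and 490–630 kcal/day at BMI 35. The effects on target and outcome trade off: the more closely delivery follows the inflated target, the less the kcal/kg difference shrinks. The article does not state the obese share. The reasons to act are correct feeding targets and a reproducible primary outcome; there is no bias between arms. It should be fixed, but it does not threaten the comparison.

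**What to change.** In section 2.6.3, replace BMI in the ideal-weight equation with a fixed reference BMI, labelled as such and given as a number from the sponsor's cited source. State that the resulting adjusted weight applies both to the bedside targets and to the per-kilogram outcomes in sections 2.7.1 and 2.7.2. In the same edit, use one cut-off, either ≥ 30 or > 30, in all three sections.

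The cost is one number and one symbol in the text. Outcomes for patients already enrolled can be recalculated from recorded energy, protein, weight and height. No new data, sample-size change or design change is needed.

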#### Ultrasound training for both groups

2.6.4

All enrolled patients will undergo ultrasound examinations on study days 1, 4, and 7. Measurements will be performed according to a standardized protocol and recorded in the case report form. Prior to enrolling the first patient, dedicated researchers who must have completed China Critical Care Ultrasound Study Group (CCUSG) training and obtained a certificate will receive ultrasound training. Ultrasound training will be conducted by certified trainers from the CCUSG. Standardized measurement protocols and instructional videos are available through the platforms https://studio.youtube.com/playlist/PL-INecaASaeDazZVy8ivoiLw0ycG0cT0_/videos.

### Study outcomes and their measures

2.7

#### Primary outcome definition and measures

2.7.1

Energy intake on Day 7, defined as the actual caloric intake on study Day 7 (kcal/kg/day). For patients with BMI > 30 kg/m^2^, an adjusted body weight will be used.

#### Secondary outcome definition and measures

2.7.2

Protein intake on Day 7, defined as the actual protein delivered on study Day 7 (g/kg/day). For patients with BMI > 30 kg/m^2^, an AdjBW will be used.Occurrence of FI between ICU days 4–7, FI is defined as (6) present if any of the following criteria are met: ① Vomiting: any visible regurgitation of gastric contents, irrespective of volume. ② High gastric residual volume (GRV): any single GRV > 200 mL. ③ Diarrhea: ≥3 loose or liquid stools per day and stool weight >200–250 g/day or volume >250 mL/day. ④ Gastrointestinal (GI) bleeding: any intraluminal GI bleeding confirmed by gross blood in vomitus, gastric aspirate, or stool. ⑤ Insufficient enteral energy delivery: failure to achieve ≥20 kcal/kg body weight/day via the enteral route within 72 h after initiation/attempt of enteral feeding. ⑥ Cessation of enteral nutrition: enteral feeding discontinued for any clinical reason. Outcome recording. The presence or absence of FI will be assessed once per day on ICU days 4–7. In addition to the composite FI outcome, individual FI components will be reported and analyzed separately.Change in nutritional biomarkers. Defined as serum albumin and prealbumin concentrations measured on study day 1 (baseline) and day 7. Reporting values (albumin in g/L; prealbumin in mg/L) at each time point; change calculated as Day 7 − Day 1.Skeletal muscle status. Muscle mass change will be assessed using the following sonographic metrics on ICU days 1, 4, and 7 after admission: upper-limb muscle thickness; quadriceps muscle thickness; rectus femoris cross-sectional area (RF-CSA).Intestinal injury biomarkers. Between-group differences in intestinal injury markers will be evaluated using serum/plasma concentrations of D-lactate, intestinal fatty-acid binding protein (I-FABP), and diamine oxidase (DAO) on study Day 1 and Day 7. *Measurement & reporting:* assays performed per manufacturer instructions; values reported in assay-specified units. Changes from baseline (Day 7–Day 1) and between-group differences in change will be analyzed.New infections in the ICU: Defined as infections newly acquired ≥48 h after ICU admission.ICU length of stay.Ventilator-free days: Ventilator-free days within 28 days in the ICU.ICU hospitalization cost. Defined as the total direct medical cost accrued during the index ICU stay, from ICU admission (time 0) to ICU discharge. Extracted from the hospital billing system/financial data warehouse using patient identifiers and ICU encounter numbers.28-day mortality: Assessed on day 28 after ICU admission.90-day mortality: Assessed on day 90 after ICU admission.

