### Randomization and blinding methods

2.4

Because all enrolled patients initially present with AGI grade I–II, a PBF will be administered for the first 3 study days. On day 4 of the study, gastrointestinal function will be reassessed. Patients reassessed as AGI grade 0–I will be eligible for randomization. Eligible patients will be randomized using block randomization, with a 1:1 allocation ratio to either continued a PBF (PBF group) or transition to an SPF (SPF group). The randomization sequence will be generated in R software (version 4.4.2) using permuted blocks of variable size (4 and 6).

Owing to the nature of the intervention, this is an open-label protocol, and the treating clinical team must be aware of group assignment for intervention delivery (participants may or may not be aware depending on clinical status). To minimize detection bias, feeding intolerance and other outcomes will be assessed and recorded by dedicated research staff who are independent from the ICU clinical team and do not participate in treatment decisions or nursing care.

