##### Exposure metrics

2.7.5.1

All participants receive a short-peptide formula from enrollment through study Day 3; this run-in period is not included in exposure analyses and is used solely for baseline standardization and tolerance assessment. Randomization occurs on Day 4 (D4). The exposure assessment window is D4–D7. We will record:

Duration of the exposure window (hours): elapsed time from randomization (D4) to 23:59 on D7 or to ICU transfer/discharge or death, whichever occurs first.Concordant feeding hours: cumulative hours during which the randomized formulation was actually administered.Adherence (%) = (concordant feeding hours ÷ exposure window hours) × 100. Interruptions (e.g., procedures, intolerance) will be time-stamped; calculations use actual accrued hours within the window.

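### Feeding-intolerance criterion 5 is timed from the start of feeding, not from randomisation, so run-in failures on the common formula count as outcomes; the day clocks for feeding intolerance and new infections also admit pre-randomisation events

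*Protocol article*

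**What the plan says.** Secondary outcome definition and measures introduces the outcome thus: "Occurrence of FI between ICU days 4–7, FI is defined as (6) present if any of the following criteria are met". The fifth criterion is "failure to achieve ≥20 kcal/kg body weight/day via the enteral route within 72 h after initiation/attempt of enteral feeding". On recording it says: "The presence or absence of FI will be assessed once per day on ICU days 4–7". It adds that "individual FI components will be reported and analyzed separately", so criterion 5 is also a treatment comparison in its own right. No wording limits FI to new or post-randomisation events.

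Randomization and blinding methods states that "a PBF will be administered for the first 3 study days", with reassessment on study day 4 and randomisation of patients at AGI grade 0–I. No intake condition is attached. Exposure metrics starts the exposure window at randomisation and sets the run-in aside for exposure analyses. The FI outcome has no matching rule.

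New infections in the ICU, another secondary outcome, are "Defined as infections newly acquired ≥48 h after ICU admission".

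**The concern.** A randomised comparison of tolerance should count events that the allocated formula could have caused. Criterion 5 mostly or wholly describes what happened before allocation. It fails in two directions:

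- A patient who missed the intake threshold during the run-in is FI-positive whatever happens afterwards.
- A patient who reached the threshold during the run-in, and falls below it only after the switch, is not picked up by criterion 5.

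The stake is a diluted comparison. A small FI difference could be read as showing that switching formula is equally well tolerated, when part of the composite could not respond to the switch. The separately reported criterion-5 result would be hard to read as a treatment effect at all. The same timing question applies to the ICU-day FI window and to the starting point for new infections.

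**Working it through.** **Inputs from the protocol**
- Criterion 5 lasts 72 h from the start of enteral nutrition (EN) (Secondary outcome definition and measures).
- EN can be started within 24–48 h of ICU admission (Inclusion criteria).
- The common run-in covers study days 1–3, with randomisation on study day 4 (Randomization and blinding methods; Study interventions; Exposure metrics).
- The FI window is ICU days 4–7, that is, hours 72 to 168 after admission.
- Infections count from hour 48.
- Sample size gives Day-7 intake of 22.4 ± 9.825 (SPF) and 24.9 ± 9.1 kcal/kg/day (PBF), and 225 per group.

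**Not in the protocol:** any FI rate, or the share q of randomised patients who fail criterion 5 in the run-in. There is therefore no stated FI figure to reproduce.

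**Step 1: which clock?** The text does not settle it.
- The ultrasound scans are on study days 1, 4 and 7 in the ultrasound training section and on ICU days 1, 4 and 7 in the secondary outcomes.
- The primary endpoint falls on study Day 7 in its definition and on ICU Day 7 in the Discussion.
- The abstract places the switch on ICU day 4; the methods place it on study day 4.

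Both readings are worked below. Let t be the hours from admission to EN start.

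**Step 2a: study day 1 is the first feeding day.** Study day 4 begins at t + 72, and criterion 5 closes at t + 72, so it is settled at about randomisation (or a few hours into day 4 if day 1 is a calendar day).

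| t | Study day 4 begins | Lead of FI window (start minus 72) | Study days 4–7 in hours | Not covered by ICU days 4–7 |
|---|---|---|---|---|
| 24 h | 96 h (ICU day 5) | 24 h | 96–192 | study day 7 |
| 48 h | 120 h (ICU day 6) | 48 h | 120–216 | study days 6–7 |

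**Step 2b: study days equal ICU days.** Day 4 begins at hour 72 and the FI window matches the exposure window. Criterion 5 still has 72 − t hours before day 4 and t hours after it: 48 and 24 h at t = 24, and 24 and 48 h at t = 48. If EN starts at about admission (t near 0), all 72 h precede day 4.

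**Step 3: infections.** The pre-randomisation time counted is (start of day 4) − 48. This is 72 − 48 = 24 h if study days equal ICU days, and 96 − 48 = 48 h to 120 − 48 = 72 h otherwise. It is positive on either clock.

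**Step 4: dilution.** Let p be the post-randomisation FI risk in an arm and r the same risk among run-in failers. The recorded risk is p + q(1 − r). With D the true arm difference, the recorded difference is D − q(r_SPF − r_PBF).
- If run-in failure is independent of later FI, r_SPF − r_PBF = D and the recorded difference is (1 − q)D.
- If run-in failers would be FI-positive later in both arms anyway, r_SPF = r_PBF and nothing is lost.

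Illustration under independence, with assumed post-randomisation FI of 40% vs 30%, 225 per group and two-sided 0.05. Power = Φ{[Δ − 1.96√(2p̄(1−p̄)/n)] / √([P1(1−P1)+P2(1−P2)]/n)}, where P = q + (1−q)p, Δ = P1 − P2 and p̄ is the mean of P1 and P2.

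| q | Recorded FI | Difference (points) | Odds ratio | Power |
|---|---|---|---|---|
| 0 | 40% vs 30% | 10 | 1.56 | 0.605 |
| 0.2 | 52% vs 44% | 8 | 1.38 | 0.397 |
| 0.4 | 64% vs 58% | 6 | 1.29 | 0.256 |
| 0.6 | 76% vs 72% | 4 | 1.23 | 0.160 |

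With 45% vs 30% assumed instead, power is 0.910, 0.722, 0.505 and 0.312 at the same values of q.

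**Step 5: is q likely to matter?** A normal approximation to the Day-7 figures gives Φ((20 − 22.4)/9.825) = 0.40 below 20 kcal/kg/day in the SPF group and Φ((20 − 24.9)/9.1) = 0.30 in the PBF group. If run-in intake is no higher than Day-7 intake, a sizeable q is plausible. This is an inference from retrospective Day-7 data, not an estimate of q.

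**The case against.** Several stronger readings are tempting, and the document does not support them.

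- **A reader might infer that criterion 5 is always fully decided before randomisation and that the FI window always opens early.** Both need study day 1 to be the first feeding day. The protocol uses study and ICU days interchangeably in several places. If they are the same, the window aligns with the exposure window and, with EN at 24–48 h, criterion 5 is mixed rather than settled.
- **A reader might infer bias between arms.** Allocation comes after the run-in, so run-in failures balance in expectation. The effect is dilution.
- **A reader might take the power losses as findings.** They rest on assumed FI rates, an assumed q and independence. Early failers probably are more likely to have FI later, which could reduce the dilution. Only patients at AGI 0–I on day 4 are randomised, and the Discussion describes them as tolerating early peptide feeding, so q may be lower than the Day-7 figures suggest.
- **A reader might treat FI as the trial's main safety outcome.** It is one of a list of secondary outcomes. Adverse events and a safety set are handled separately, and the primary endpoint is untouched. The separate analyses of vomiting, gastric residual volume, diarrhoea, bleeding and EN cessation are not affected by criterion 5.

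These points limit the size and certainty of the problem but do not remove it. On either clock, all or part of criterion 5 precedes randomisation, any one criterion suffices, and nothing requires post-randomisation onset. The infection point does not depend on the clock.

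**Conclusion.** The point holds as a should-fix. Criterion 5 is tied to EN start, so on one clock it is settled at about randomisation, and on the other, with EN at 24–48 h, 24–48 of its 72 hours precede day 4. Run-in failures therefore enter the FI composite and make the criterion-5 component hard to interpret. If the clocks differ, the FI window also misses study day 7 (EN at 24 h) or days 6–7 (EN at 48 h). New infections include at least 24 h of pre-randomisation time on either clock.

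The consequence is non-differential dilution of a secondary outcome toward the null, by a factor of (1 − q) under independence and by less if early failers would be FI-positive later anyway. The protocol gives neither q nor FI rates, so no specific power loss can be asserted. The intake threshold itself is not in question.

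**What to change.** 1. State how study days relate to ICU days and put all outcomes on one clock. Reconcile the abstract's allowance for starting feeding within 7 days with the inclusion criterion's 24–48 h.
2. Count FI only with onset after randomisation, to the end of study day 7.
3. Take the 72 h criterion out of the FI composite and report post-randomisation enteral energy delivery as a separate outcome. Replacing it inside the composite with any post-randomisation day below the threshold is not advisable: by the Day-7 approximation, 30–40% would be positive on that day alone, so low intake, which overlaps the primary endpoint, would dominate.
4. Record failure of criterion 5 during the run-in as a baseline variable.
5. Count new infections only with onset after randomisation.

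The cost is a change of outcome wording; FI is already assessed daily, although onset times on day 4 and for infections must be available. The small downside is that the composite departs slightly from the cited definition. Only outcome counting changes; bedside management of intolerance is unaffected.
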